### Data processing

This pilot feasibility study focuses on a single group of students from the Bachelor Program at College of Health Sciences (CoHS), GMU, with a minimum sample size of 40 participants to assess the feasibility and acceptability of the approach. Given the pilot sample size (*n*=40), model evaluation will use repeated stratified k-fold cross-validation (or leave-one-out CV) and bootstrap confidence intervals to reduce instability from fixed splits. A pre–post analysis will be conducted to evaluate the significance of differences in the occurrence of high-risk students at each stage of data collection (across three time points). The third assessment point will be their final score and passing percentage. Subsequently, this study may be expanded to a larger sample size using a cluster-randomized group study design. The project will utilize Python and related libraries.

Additional automated alerts and academic advice generated by AI will be thoroughly cross-verified by the investigators with respect to the target students and mentors. In parallel, the investigators will manually analyze student performance using data from the three designated time points [human-in-the-loop governance (mentor approval and escalation)]. This process will allow the investigators to confirm the integrity, accuracy, and functionality of the newly proposed AI mentorship model. A survey will also be conducted among the targeted students and faculty to assess their responses, success rates, and the accuracy of the proposed AI co-mentoring model in tracking academic progress. The present study is designed to use quantitative data, while qualitative data from the survey will be used for validation purposes. Figure 1 provides an overview of the intended workflow in the form of a flowchart.

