Previous risk prediction models developed by researchers relied on statistical analyses and calculations that were often too complex for faculty to easily understand and apply. Hence, the current study proposes to validate both supervised and unsupervised AI mentoring, using ChatGPT-4 and a predictive risk engine (rules + ML models) to recognize students at risk and provide them mentoring advice to help achieve their learning goals.

The AI Risk Identification Assistance System (AIAS) is conceptualized as a learning analytics early-warning system integrated with mentoring practice. The risk engine identifies students who may not meet the course benchmark (e.g., <65% continuous assessment), while the mentoring layer delivers self-regulated learning (SRL)-oriented prompts and facilitates timely human follow-up at weeks 5 and 10.

The novelty and originality of this project lie in its simplicity and practical application. Earlier studies utilized complex calculations and did not deeply explore how different AI applications align with specific pedagogical models or teaching strategies across disciplines and contexts. They focused on formulas to identify at-risk students and offered automated academic advice through AI. Furthermore, these studies often lacked regular follow-up phases to track student progress and did not test AI-driven mentoring models (14, 15).

Our proposed AI mentoring model is expected not only to recognize at-risk students based on their pedagogical assessment system but also to provide personalized advice to ensure their academic success. This will be achieved through regular automated reminders, risk reports, and academic advice generated by supervised and segmentation engines (unsupervised AI models). The role of the faculty is to simply upload the necessary data to the chatbot. The study will be conducted on students from Health Science at the College of Health Sciences, Gulf Medical University (GMU), UAE, for a semester.

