### A sample risk assessment summary by a supervised AI system

A sample CHATGPT-4 automated risk report with a message generation layer [templated or large language model (LLM)-assisted drafting; student-specific academic counseling messages] is provided in the following (Supervised AI mentoring model):

Sample Automated Risk Report by AI (Based on Analysis of Academic Performance)

Dear Student,

Subject: Academic Progress/Student at Risk/Academic Counseling

Based on the latest academic performance evaluation for the course [Course Name – Course Code], you have been identified as at risk of not meeting the passing criteria, as your current performance falls below the required benchmark.

Your academic progress as of [Date] is summarized as follows:

Attendance: 80%

Class Test: 55%

Coursework: 65%

Midsemester Exam: 65%

Total Average Score: 61.67%

[Passing benchmark: You must achieve a minimum score of 65%.]

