### Sample pedagogic AI-generated individualized academic advice/message generation layer (templated or LLM-assisted drafting) for both supervised and unsupervised models

#### Advisory—student performance

The student demonstrates moderate academic performance, with a total average of 61.7%, slightly below the required 65% pass mark. A key area for improvement is the Class Test component (55%), which indicates the need for strengthened conceptual understanding and test-taking strategies.

To improve this component and move past the 65% pass mark, consider the following:
Review key concepts regularly—Revisit lecture notes and learning materials to strengthen your understanding of core topics.Practice past papers or sample questions—This helps familiarize yourself with the question style and improve accuracy under time constraints.Clarify doubts early—Seek guidance from your course instructor or peers whenever you find a topic is unclear.Improve time management—Allocate sufficient time for each section during tests to ensure all questions are attempted.Focus on feedback—Analyze errors from previous tests to avoid repeating them in future assessments.Schedule a one-on-one mentoring session—Arrange a one-on-one meeting with your academic advisor for personalized guidance and study plans.To track individual student progress, similar reports will be generated at three different time points throughout the semester to analyze student improvement. To accomplish this, CHATGPT-4 will be programmed to notify both the mentor and the student if a student’s performance falls below the benchmark at the 5th and 10th weeks of each semester while the data are manually uploaded by the course coordinator for a given course. To support this, ChatGPT will send regular reminders over the following 2 weeks, encouraging students to take necessary actions to enhance their performance and meet the eligibility criteria for the end-semester examinations.

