A sample risk identification category was developed to train ChatGPT-4 using structured prompts, enabling the text-generation service to draft mentoring messages from deidentified student performance summaries. An example of the risk profile generated by the unsupervised AI clustering system is presented in Tables 1 and 2. The authors plan to notify students of their cumulative grade point average (CGPA) scores as they transition from one semester to the next (Tables 3, 4) in order to keep the students informed of their academic achievements at each stage. This feature allows students to assess their progress, take proactive steps to improve, or maintain a strong CGPA.

**Table 1 T1:** Sample risk profile identified by an unsupervised AI system.

Area	Performance indicator	Risk level	Comments
Assignment submission	3/5 submitted	High	Two assignments are missing or late
Class attendance	62%	High	The following required 75% attendance
Practical test performance	45%	Medium	Needs improvement in learning demos of hands-on skills
Class test performance	68% average	Medium	Borderline performance
Participation and engagement	Low	High	Rarely engages in class discussions

**Table 2 T2:** Sample performance metrics of a supervised AI risk predictive model.

Assessment component 1 (20% weightage)			Assessment component 2 (20% weightage)			Assessment component 3 (25% weightage)			Analysis and risk identification	
Class test			Coursework			Midsemester Exam			Summative score 65 (excluding End-Semester Exam)	Risk category/performance appraisal
Score above 80% out of 20 (>16)	Score >70%but <80% out of 20 (>14)	Score <60% out of 20 (<12)	Score above 80% out of 20 (>16)	Score >70%but <80% out of 20 (>14)	Score <60% out of 20 (<12)	Score above 80% out of 25 (>20)	Score >70%but <80% out of 25 (>17.5)	Score <60% out of 25 (<15)	Score above 80% out of 65 (>52)	Above average^a^
									Score >70%but <80% out of 65 (>45.5)	Moderate risk: Meet your mentor for appropriate counseling^a^
									Score <60% out of 65 (<39)	High risk. Recommended for rigorous mentor advice, additional remedial measures, and follow-up^a^

^a^
Students will receive an automated checkpoint-based risk classification report at weeks 5 and 10 from chatbot.

**Table 3 T3:** Risk predictive model for the CGPA score.

Program/year/class	Evaluation component		Analysis and risk identification	
	GPA scores secured by students	GPA score conversion to percentage	Risk category	
			90–100	Satisfactory^a^
			85–<90	

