#### Sample size and power considerations

Formal power calculations were not performed, as the study was not designed to test hypotheses or estimate diagnostic performance with precision. Instead, the sample size was determined by cohort availability, consistent with pilot-study methodology.

Confidence intervals were reported for agreement statistics to provide transparency regarding sampling variability and interpretability limits. All findings are therefore considered hypothesis-generating and intended to inform the design of larger, adequately powered confirmatory studies.

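### The pre–post analysis tests change in high-risk status only, a cut of marks already held, and so loses information on within-student change; a paired analysis of the marks is a cheap improvement

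*Protocol article*

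**What the plan says.** All places are in the protocol article.

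- **Data processing** gives the change analysis: "A pre–post analysis will be conducted to evaluate the significance of differences in the occurrence of high-risk students at each stage of data collection". It covers three time points: weeks 5 and 10, and then a last one, "The third assessment point will be their final score and passing percentage". The group is a single cohort "with a minimum sample size of 40 participants to assess the feasibility and acceptability of the approach".
- **Advisory—student performance** gives the purpose of the repeated reports: "similar reports will be generated at three different time points throughout the semester to analyze student improvement".
- **Table 2** sets high risk on the 65-mark summative total, which excludes the end-semester exam, as "Score <60% out of 65 (<39" marks). The Introduction uses another threshold: "The risk engine identifies students who may not meet the course benchmark (e.g., <65% continuous assessment").
- **The sample risk report** shows that each student's numeric result is available, for example "Total Average Score: 61.67" percent, together with the component percentages behind it.
- **Statistical analysis** covers descriptive feasibility results, agreement and resampling. It does not mention the pre–post comparison or any analysis of change in the mark.
- **Sample size and power considerations** says: "Formal power calculations were not performed, as the study was not designed to test hypotheses or estimate diagnostic performance with precision".

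**The concern.** The reports are meant to show whether students improve, but the one stated comparison over time looks only at whether students are above or below a line. With a 60% cut, a student who goes from 45% to 58%, or from 61% to 69%, counts as unchanged. In a paired comparison of a yes/no status, only those who cross the cut carry information, and in a cohort of 40 these are few.

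At stake is the usefulness of this one comparison. A real rise of several marks could be reported as no significant difference. The stated analysis also would not supply the mean change and its spread, which would help plan the cluster-randomised expansion that the article foresees. The concern stands even if the same score is used at every time point.

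**Working it through.** **Inputs from the article.** n = 40, the same students over time; high-risk cut 39/65 = 60%; other benchmark 65%. There is no design figure to reproduce: no power, SD, correlation, effect or high-risk rate is given.

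**Assumptions.** Marks bivariate normal; mean 68 or 72%; SD 10 or 12 points; correlation between two time points 0.5, 0.7 or 0.8; two-sided 5%; 20,000 simulated cohorts per scenario. The article names no test. McNemar is used as the natural paired test for a yes/no status, in exact and mid-p form, against a paired t-test on the mark.

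**1. Central case (mean 68, SD 12, correlation 0.7, every student +5).**
- Marks: SD of the difference = 12 × √(2 × (1 − 0.7)) = 9.30. Standardised change = 5/9.30 = 0.538. Noncentrality = 0.538 × √40 = 3.40. Simulated power is 91%.
- Status at the 60% cut: expected high-risk students fall from 40 × Φ((60 − 68)/12) = 10.1 to 40 × Φ((60 − 73)/12) = 5.6. In simulation about 6.1 students leave the high-risk group and 1.6 enter it, so about 8 cross. Power is 24% (exact) or 34% (mid-p).
- Why it is so low: with 8 crossings, a 7–1 split gives exact p = 2 × 9/256 = 0.070, so only 8–0 is significant (2 × 1/256 = 0.008). With 5 crossings or fewer no split reaches 5% (2 × 0.5⁵ = 0.0625).

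**2. Every student gains 3 or 5 points, whole range.**

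| Analysis | Power |
|---|---|
| Paired marks | 33–100% |
| Exact McNemar, 60% cut | 3–28% |
| Exact McNemar, 65% cut | 9–54% (11–54% at mean 68, 9–35% at mean 72) |

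The smallest advantage of the marks is 23 points over exact McNemar and 18 over mid-p.

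**3. Only students below the benchmark gain.**

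| Who gains 5 or 8 points | Paired marks | Exact McNemar | Mid-p McNemar | Advantage over mid-p |
|---|---|---|---|---|
| Below 65% at the first point | 10–63% | 3–33% | 6–45% | about 2–25 points |
| Below 60% at the first point | 6–28% | 2–13% | 4–19% | about 1–13 points |

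**4. Check by a second route.** For a small uniform shift, the efficiency of paired status relative to paired marks is [φ(c)²/D] × 2(1 − ρ), where c is the normal cut-point for the high-risk rate, D the proportion who cross with no shift, and ρ the correlation. At a 20% rate and ρ = 0.7: φ(−0.842)² = 0.078 and D = 0.174, so 0.078/0.174 × 0.6 = 0.27. Forty students then carry the information of 40 × 0.27 ≈ 11. For ρ from 0.5 to 0.85 and rates from 10 to 50%, efficiency is 12–48%. It passes 50% only with weak correlation and rates of 30% or more.

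**5. Three time points.** With ρ = 0.7 and a total gain of 0.4 SD, power is about 83% for a repeated-measures analysis of marks. Cochran's Q on status gives 24% at a 20% rate and 36% at a 40% rate.

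**The case against.** - **The effect may not be cohort-wide.** Alerts go to students below the benchmark, and Table 6 gives no outreach where no risk is identified (although the footnote to Table 2 sends a classification report to every category). A mean over 40 students dilutes a gain confined to a minority. This stands. A reader might infer that the plan discards most of its ability to detect change in performance; the documents do not support that in general. It holds for a shift across the whole cohort, and step 3 shows how far it shrinks otherwise.
- **Power is not an aim here.** The comparison is neither a primary outcome (feasibility, acceptability) nor a secondary one (agreement), and the article disclaims hypothesis testing. This limits the weight of the point. But Data processing still plans an evaluation of significance, and an estimate with an interval suits the disclaimer better than a weak test.
- **High-risk status is a legitimate target**, since it triggers mentoring. This stands, and is a reason to keep it as a reported result.
- **Not every label is a cut of one mark.** Table 1 rates missing assignments and low participation, Table 6 uses sustained disengagement, and Data processing does not say which label is counted. So the argument applies to the summative mark in Table 2, and not necessarily to every risk label.
- **The article is condensed and names no test.** A reader might infer that change in marks will never be estimated. The text does not show that: investigators are also to analyse performance manually at the three time points. The point is that the one comparison the article does fix is the less informative one.
- **The scores may not be comparable.** The third point is a final score, while Table 2's total leaves out the end-semester exam. This stands as a condition on the fix. It does not favour the status, which would be cut from the same scores.

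**Conclusion.** The point holds in a limited form. The only stated pre–post analysis uses a yes/no status that, on the summative mark, is a cut of a score already held, and it loses information on within-student change. The paired mark was ahead in every scenario run. The advantage is large if the whole cohort improves (91% against 24% exact or 34% mid-p in the central case). It is small to moderate if only below-benchmark students improve, when both analyses can be too weak to be useful.

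These figures rest on assumed means, SDs, correlations, effects and normality, and on McNemar as the test. Because the comparison is exploratory and outside the listed outcomes, this is a modest and inexpensive improvement. It does not invalidate the study or its primary results.

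**What to change.** In Data processing, replace the significance evaluation with wording along these lines:

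- The main pre–post result is the mean within-student change in continuous-assessment percentage, with a 95% confidence interval.
- The score has the same composition at each time point compared: weeks 5 and 10, and the final point only on a comparable percentage that excludes the end-semester exam. If some components are not complete at week 5, compare only those present at both points.
- Use a paired difference for two time points, or a linear mixed model with a student random effect for three.
- Report the high-risk proportion at each time point, with confidence intervals and a transition table, as a companion descriptive result. State which risk label is counted.

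This also brings Data processing into line with the statement that the study was not designed to test hypotheses.

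**Cost.** A few sentences and a few lines of Python, with no extra students. The marks are already held, but someone must confirm that a like-for-like percentage can be built. The article sends protocol amendments to the ethics committee.

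**Downside.** Mean change is less directly tied to the mentoring trigger, which is why the proportion stays. In a single uncontrolled group, neither analysis separates mentoring from time or regression to the mean, and the report should say so.

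### The pre–post significance test of high-risk occurrence ends on a different score from the one it starts on, and it contradicts the statement that no hypotheses are tested

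*Protocol article*

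**What the plan says.** The plan for this comparison, which spans three time points, is in the Data processing section of the protocol article. The aim of the pre–post analysis there is to "evaluate the significance of differences in the occurrence of high-risk students at each stage of data collection". It is made in a single group with a minimum of 40 students. The next sentence fixes the last of the time points: "The third assessment point will be their final score and passing percentage".

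The first two points are the week-5 and week-10 checkpoints. The footnote to Table 2 reads "Students will receive an automated checkpoint-based risk classification report at weeks 5 and 10 from chatbot". The score behind that table is headed "Summative score 65 (excluding End-Semester Exam"), made up of class test (20), coursework (20) and midsemester exam (25). Its high-risk row is "Score <60% out of 65 (<39").

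The sample risk report uses another threshold as its passing benchmark: "You must achieve a minimum score of 65"%.

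The section on sample size and power considerations says that "the study was not designed to test hypotheses or estimate diagnostic performance with precision". The Statistical analysis section describes descriptive summaries, agreement statistics and resampling. It contains no pre–post comparison.

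**The concern.** A pre–post comparison of a proportion is interpretable only if the same event is counted each time. Here the checkpoint event is a score below 60% of 65 in-course marks. The third-point measure is a final score, which brings in an exam that the checkpoint score leaves out, together with a pass rate. The article gives no high-risk rule for the final score. If the pass mark is used, both the score and the threshold change between week 10 and the end.

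A difference in high-risk counts could then come from the definitions, the difficulty of the exam or the threshold. With no comparator, none of these can be separated from an effect of the mentoring. The Discussion expects the study to inform on the impact of AI in student support and anticipates better retention and success, so a significant change in either direction is likely to be read as evidence about the intervention. The article also both plans a significance evaluation and says that the design does not test hypotheses. These two statements cannot both stand.

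**Working it through.** The documents give no rate, alpha, power or score distribution for this comparison, so there is no stated figure to reproduce. The Table 2 arithmetic is consistent: 60%, 70% and 80% of 65 are 39, 45.5 and 52.

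**Inputs from the documents.** n = 40; checkpoint weights 20/20/25 out of 65; high-risk cut 60%; pass mark 65%. Table 2 is taken as the checkpoint label. Tables 3 and 4 carry high-risk categories of their own for CGPA and attendance, and Data processing does not say which table it means.

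**Assumptions not in the documents.** Each component has mean 70 and SD 12; any two components correlate at r = 0.4; scores are normal; the End-Semester Exam carries 100 − 65 = 35 marks and is as hard as the rest; the intervention has no effect.

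**Step 1: spread of each score.** For weights w summing to 1, let s = Σw². Then SD = 12 × √(s + r(1 − s)).
- 65-mark score: s = (20² + 20² + 25²)/65² = 1425/4225 = 0.337. SD = 12 × √(0.337 + 0.4 × 0.663) = 9.31.
- Final score: s = 0.20² + 0.20² + 0.25² + 0.35² = 0.265. SD = 12 × √(0.265 + 0.4 × 0.735) = 8.97.

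**Step 2: expected high-risk students out of 40.**
- 65-mark score below 60%: Φ(−10/9.31) = 0.141, or 5.7 students.
- Final score below 60%: Φ(−10/8.97) = 0.133, or 5.3 students.
- Final score below 65%: Φ(−5/8.97) = 0.289, or about 11.5 students.

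Keeping the cut moves the count by about 0.4 of a student. Switching to the pass mark roughly doubles it.

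**Step 3: how often a paired test would be significant.** Exact McNemar with all movement in one direction needs six movers: 2 × 0.5⁶ = 0.031, whereas 2 × 0.5⁵ = 0.0625. In simulated cohorts of 40 with no effect:
- 60% cut kept: about 1.6 students leave and 1.3 enter the high-risk group per cohort; significant in about 0.2% of cohorts.
- 65% pass mark at the third point: about 6.1 enter and 0.2 leave; significant in about 52% of cohorts. Over r = 0.3 to 0.6 and mean 68 to 72, the range is about 31% to 67%.

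**Step 4: direction.** A second null model used a true level with SD 8, independent component error with SD 8, a 60% cut throughout and an exam 8 points easier than the other components. The rate then falls from the 65-mark score to the final score. With mean 70 it goes from about 14% to 8% (McNemar significant in about 3% of runs). With mean 65 it goes from about 29% to 19% (about 20% of runs). In the same model with mean 70, equal difficulty and the 65% pass mark, it rises from about 14% to 29% (about 55% of runs).

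**The case against.** The comparison is one sentence. The primary outcomes are feasibility and acceptability, analysed descriptively, and the secondary outcomes are agreement statistics; the pre–post comparison is in neither list. An article may leave the exact paired test and the third-point rule to a fuller protocol or analysis plan. The section on sample size and power already calls all findings hypothesis-generating, and the limitations name the single institution and cohort. This lowers the severity. It does not remove the point, because the article itself fixes the third measure as something other than the checkpoint score, and itself makes both of the conflicting statements about testing. Nowhere does it say that a change cannot be attributed to the mentoring.

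Three stronger readings are tempting but unsupported.
- A reader might infer that the high-risk share must fall by construction, through averaging more marks and regression to the mean. Steps 2 to 4 show little change, a rise or a fall, depending on the cut and the exam difficulty, and the documents fix neither.
- A reader might infer that weeks 5 and 10 also use different scores, because fewer components may exist early. The same tables are named for both weeks, and nothing says which components are available at week 5. If the class test alone were used then, the expected count would be 40 × Φ(−10/12) = 8.1, and the fall to the final score at the 60% cut would be 8.1 − 5.3 = 2.8 students. Of that, 8.1 − 5.7 = 2.4 would rest on this inference alone.
- A reader might infer that the AI label will be validated against a final score that contains the same marks. No such correlation is planned: the stated comparator is faculty-assigned categories, and faculty assessment is the reference standard.

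**Conclusion.** The concern holds in two parts, both plain from the text. First, the third time point is not the variable measured at the checkpoints, so a change in the high-risk rate can arise from the definitions alone, in either direction. Second, evaluating significance conflicts with the statement that the study does not test hypotheses, and the test is absent from the Statistical analysis section.

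The size depends on choices that the article leaves open. It is negligible from week 10 to the end if one cut is kept and the exam is equally hard. It is large if the pass mark becomes the third-point criterion. The score distributions, the correlation and the 35-mark exam weight are assumptions, so the figures illustrate what can happen and do not forecast it. This should be fixed; it does not threaten the primary or secondary outcomes.

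**What to change.** Revise the Data processing paragraph as follows.
- Restrict any comparison of high-risk occurrence to time points that share one stated high-risk rule and the same score content.
- Report the final score and pass rate separately, as an end-of-course description and not as a third value of the same outcome.
- Have the authors reconcile the 60% high-risk cut in Table 2 with the 65% benchmark in the sample report, and say how each relates to the label being counted. No view is taken here on which is right.
- Replace the significance evaluation with paired proportions and the difference between them, with 95% confidence intervals. Alternatively, keep a named paired test, list it under Statistical analysis and amend the sample-size statement to match.
- State that no change over time can be attributed to AI mentoring in a single-group design.

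These are changes of wording and need no new data. The cost is the loss of a p-value (if the test is dropped) and of a like-for-like third point, and with them a weaker claim about impact. They should be made before recruitment in Academic Year 2026.
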